#### 2.8.2. Verum Acupuncture Group 1 (VA1)

Participants assigned to the VA1 will receive 12 acupuncture sessions over 4 weeks, that is, 3 days/week. A telephone interview will take place two weeks after the end of treatment to collect data on the severity of pruritus symptoms, amount of TCS used, and adverse effects. Participants' final visit will occur 4 weeks after the end of treatment. No other intervention will be permitted during the study period.

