#### 2.8.3. Verum Acupuncture Group 2 (VA2)

Participants assigned to the VA2 will receive 8 acupuncture sessions over 4 weeks, that is, 2 days/week. A telephone interview will be given two weeks after the end of treatment to collect data on the severity of pruritus symptoms, amount of TCS used, and adverse effects. Participants' final visit will occur 4 weeks after the end of treatment. No other intervention will be permitted during the study period.

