#### 2.8.4. Sham Acupuncture Group (SA)

Participants assigned to the SA group will receive 8 acupuncture sessions over 4 weeks, that is, 2 days/week. Sham acupuncture treatment will be conducted on 6 control points: a point 1 to 2 cm proximal and 1 cm medial to LI7, a point 1 cm proximal and 1 cm medial to LI11, and a point 1 cm proximal and 1 cm lateral to ST36, each bilaterally. Instead of intradermal needles, the same sized stainless steel rings without needles, that is, nonpenetrating intradermal needles, which were designed and validated for blinding for our study, will be attached to three control points: a point 1 cm proximal and 1 cm medial to LI11, bilaterally, and finger point in the ear, contralaterally [25]. Unlike VA1 and VA2, fixed acupuncture treatments will be given, but questions about symptoms, TCS, and adverse effects will be asked to participants in this group. A telephone interview will also be given two weeks after the end of treatment to collect data on the severity of pruritus symptoms, amount of TCS used, and adverse effects. After the 4-week treatment period, participants will return for a final visit at 4 weeks after the end of treatment, identical to VA1 and VA2.

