#### 2.11.2. Statistical Analysis Plan

We will perform descriptive analyses for all outcome measures. Categorical variables will be provided with percentages, and continuous variables will be provided as means with standard deviations. An independent statistician will perform statistical analyses using SPSS 21.0 (IBM SPSS Statistics, New York, USA). Missing data will be replaced by carrying forward the most recent nonmissing value, and the time and reason for the missing data will be recorded. Depending on the recorded reasons, multiple imputation by an independent statistician will be done and compared.

The effectiveness of the intervention will be provided by examining changes in outcome measures between baseline and end of treatment and through the follow-up period, using a repeated measures analysis of variance (ANOVA) and *χ*^2^ test. The difference in effect between VA1 and VA2 will be analysed by examining changes in the itch VAS and SCORAD index, by the Mann–Whitney *U* test on continuous variables and *χ*^2^ test on categorical variables. The difference in therapeutic effect between VA (using the most efficacious dose between VA1 and VA2) and SA will be investigated in the same way. The data will be analysed with a *p* = 0.1 (two-sided) statistical significance level and 90% confidence intervals will be provided following the statistician's advice for a small sample size. The current data will be used to calculate the number of participants needed to reach a significance level of 0.05 and 80% power.

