A battery of outcome measures will be used in our study since it is exploratory in nature. We will investigate the effects of acupuncture treatment on AD symptom improvement with a particular focus on antipruritic effect, measured using itch VAS, SCORAD, EASI, and POEM. Information on rescue medication use and quality of life will also be collected. For pattern identification in Korean Medicine, the AD pattern and Cold-Heat questionnaires, along with PPT, will be administered. CES-D and STAXI will examine potential anxiolytic and stress-relieving effects of acupuncture. Through credibility testing, the feasibility of participant blinding to treatment assignment will be thoroughly examined. Some may argue that nonspecific effects may unnecessarily increase in our trial by the increased attention due to a variety of outcome measures. The outcome measures, however, will be given to the participants in all three groups which will make it unlikely for one specific group to experience a larger nonspecific benefit due to the increased attention. We will nevertheless carefully examine whether there will be additional nonspecific benefits in any group and the feasible outcome measures will be selected to work for a main trial. Finally, our study will provide valuable data regarding treatment of AD with acupuncture, but also relative to identifying potential biomarkers associated with its development.

Establishing an adequate sham control is essential in an RCT of acupuncture. We will utilise a nonpenetrating sham acupuncture and nonpenetrating intradermal needles as a control group, which receive sham treatment twice a week for 4 weeks. There has been a long debate about the specific effect of acupuncture: acupuncture works mainly via a placebo effect [70]; or tested sham acupuncture controls so far may not be completely inert [71, 72]. The sham control in our study was designed to minimise a specific physiological effect that may be induced by needle insertion and to avoid specific acupuncture points in the body and the ear. In addition, the number of treatment sessions in the control group was set as twice weekly to minimise other nonspecific benefits such as doctor-patient interaction and the Hawthorne effect; this is feasible due to appropriate blinding techniques.

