*(3) Treatment regimen*	*(3a) Number of treatment sessions* (i) 8 or 12 sessions according to the allocated group *(3b) Frequency and duration of treatment sessions* (i) Twice or 3 times a week for 4 weeks, 20 minutes for each session

*(4) Other components of treatment*	*(4a) Details of other interventions administered to the acupuncture group (e.g., moxibustion, cupping, herbs, exercises, lifestyle advice)* (i) Lifestyle advices will be given to all participants (ii) Corticosteroids will be allowed as a rescue medicine of severe pruritus through the consensus of the KMD in charge of this study and the pharmacist working for Kyung Hee University Korean Medicine Hospital *(4b) Setting and context of treatment, including instructions to practitioner and information and explanations to patients* (i) A university hospital (ii) Participants will be informed about acupuncture treatment in the study as follows: “In this study, you will be randomly allocated to verum acupuncture treatment or sham acupuncture treatment and acupoints for AD will be selected based on traditional Korean medicine textbook and AD-related reports. Also, additional acupoints can be used according to individual conditions.”

*(5) Practitioner background*	*(5) Description of participating acupuncturists (qualification or professional affiliation, years in acupuncture practice, other relevant experience)* (i) A KMD who has a license and at least two years of clinical experience in dermatologic disorders. He attended 10 hours of training and simulation workshop to ensure that he is able to provide identical acupuncture treatment in accordance with a predefined protocol

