●: conducted on every participant of this study, both AD patients and healthy controls; ○: conducted on AD patients of this study, not on healthy controls; ⊗: conducted on AD patients, but with different frequency on groups. That is, VA1 receives acupuncture treatment or checks adverse events 3 days a week, VA2 2 days a week, and SA 2 days a week; ☏: a telephone interview will be conducted on AD patients of this study, not on healthy controls; AD, atopic dermatitis; CES-D, Center for Epidemiologic Studies-Depression Scale; Cold-Heat, cold-heat pattern identification based on diagnosis in Traditional Korean Medicine; DLQI, Dermatology Life Quality Index; EASI, Eczema Area and Severity Index; POEM, Patient Oriented Eczema Measure; PPT, Pain Pressure Threshold; SCORAD, SCORing Atopic Dermatitis; STAXI, state-trait anger expression inventory; TCS, topical corticosteroid.

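### If the three-times-weekly verum arm is the one compared with sham, the contrast mixes needling with four extra therapist sessions (12 against 8)

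*Protocol article*

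**What the plan says.** The session numbers are in Protocol article, sections 2.8.2 to 2.8.4:

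- VA1: "Participants assigned to the VA1 will receive 12 acupuncture sessions over 4 weeks, that is, 3 days/week".
- VA2: "Participants assigned to the VA2 will receive 8 acupuncture sessions over 4 weeks, that is, 2 days/week".
- SA: "Participants assigned to the SA group will receive 8 acupuncture sessions over 4 weeks, that is, 2 days/week".

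Table 1, item 3b, gives the session length for all arms: "Twice or 3 times a week for 4 weeks, 20 minutes for each session". Section 2.8.1 has one practitioner giving every treatment, and section 2.7 says that treating practitioners cannot be blinded. The footnote to Table 2 shows that safety checks follow the same pattern: "VA1 receives acupuncture treatment or checks adverse events 3 days a week, VA2 2 days a week, and SA 2 days a week".

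The Discussion gives the reason for the sham frequency: "the number of treatment sessions in the control group was set as twice weekly to minimise other nonspecific benefits such as doctor-patient interaction". It adds the Hawthorne effect as a second thing to be held down, and says that blinding makes the choice feasible.

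The verum arm that meets the sham is not fixed. Section 2.11.2 sets the therapeutic contrast as "VA (using the most efficacious dose between VA1 and VA2) and SA". Section 2.10.14 makes the same choice for the microRNA comparison at 4 weeks, which is meant to find markers related to the acupuncture effect.

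**The concern.** A sham arm isolates the effect of needling only if the arms are alike in everything else that can produce improvement, including the amount of time with a therapist. In VA1 versus SA the arms differ in both needling and number of contacts. The Discussion presents the lower sham frequency as protection against nonspecific benefit. For this contrast it does the opposite, because whatever the four extra sessions contribute without needling is added to the verum-minus-sham difference. This holds even if every participant stays fully blinded, since a blinded participant still attends 12 times or 8 times.

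The selection rule brings the problem into the analysis. Any benefit from extra contact raises the chance that VA1 looks better than VA2, and so is carried forward, and it also raises the VA1–SA difference that is then reported. Section 2.11.1 plans to use the effect sizes for itch VAS and SCORAD to power a large trial, so an inflated estimate would be passed on. The microRNA contrast would have the same ambiguity.

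**Working it through.** **Session counts.** Inputs: sections 2.8.2 to 2.8.4.

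- VA1: 3 per week × 4 weeks = 12, as stated.
- VA2 and SA: 2 per week × 4 weeks = 8 each, as stated.

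**Contact in each contrast.** Session length of 20 minutes from Table 1, item 3b.

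| Contrast | Planned sessions | Ratio | Minutes |
|---|---|---|---|
| VA1 v SA | 12 v 8 | 1.50 | 240 v 160 |
| VA1 v VA2 | 12 v 8 | 1.50 | 240 v 160 |
| VA2 v SA | 8 v 8 | 1.00 | 160 v 160 |

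At the minimum for compliance in section 2.9 (10 of 12 in VA1, 6 of 8 in VA2 and SA), VA1 versus SA becomes 10/6 = 1.67.

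**Size of a possible bias (illustration).** The documents give no figure for a contact effect. Assume that 8 sessions of contact alone yield s = 0.25 to 1.0 SD of improvement, proportional to sessions. The four extra sessions are then worth b = s × 4/8 = 0.125 to 0.5 SD. Take no needling effect, normal outcomes and the plan's two-sided level of 0.1. The number per arm is 30/3 = 10, or 10 × 0.8 = 8 after the 20% dropout in section 2.11.1.

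Chance of p < 0.1 for VA1 versus SA, using the exact Mann–Whitney test (the test named in section 2.11.2; simulated), with the t test for comparison:

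| b (SD) | Mann–Whitney, n = 10 | Mann–Whitney, n = 8 | t test, n = 10 |
|---|---|---|---|
| 0 | 9% | 8% | 10% |
| 0.125 | 10% | 9% | 11% |
| 0.25 | 13% | 12% | 15% |
| 0.375 | 19% | 16% | 21% |
| 0.5 | 26% | 21% | 29% |

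The Mann–Whitney reference is below 10% because its p-values are discrete. At n = 10 the exact size is 8.9%; at n = 8 it is 8.3%.

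**Chance that VA1 looks better than VA2.** The difference of two means of 10 has SD √(2/10) = √0.2, so the chance is Φ(b/√0.2). For b = 0.125, 0.25, 0.375 and 0.5 this is 61%, 71%, 80% and 87%. It is 50% with no contact effect.

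**The case against.** Several points on the other side stand.

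- **A matched pair already exists.** VA2 has the same 8 sessions as SA, so the sham arm did not get less contact than every verum arm. The problem is confined to VA1, and arises because no section reserves the sham claim for VA2.
- **The Discussion does not contradict itself on attention.** A reader might set the sentence "which will make it unlikely for one specific group to experience a larger nonspecific benefit due to the increased attention" against the 12-versus-8 schedule. But the sentence before it limits the subject to attention arising from the outcome measures, and in Table 2 those have the same timing in all three arms. Within that scope the statement is correct. It simply does not reach treatment sessions.
- **VA1 versus VA2 is largely framed properly.** Sections 2.1 and 2.2 and the Discussion speak of dose and schedule, of weekly frequency and of regimen. For that practical question extra visits are part of what is compared. A reader might infer a claim about needling dose apart from visits, but the article makes none.
- **The issue is partly acknowledged.** The Discussion promises to look for additional nonspecific benefit in any group. It names no method, and without a 12-session sham arm the effect of contact cannot be separated from needling within VA1.
- **The trial is exploratory.** It is a feasibility study with no designated primary outcome, and the bias matters only if VA1 is selected. The assumed contact effect is not from the documents, and at its low end the rejection rate hardly moves.

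These points limit the reach and weight of the concern. They do not rescue the stated rationale or the open choice of verum arm.

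**Conclusion.** The concern holds for contrasts that use VA1. If VA1 is selected, the sham comparison and the microRNA comparison carry 1.5 times the therapist sessions on the verum side, and a difference cannot be credited to needling alone. The Discussion's reason for the sham frequency is wrong for that contrast.

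The session counts are certain; the size of the bias is not. Under the assumed 0.125 to 0.5 SD, proportional to sessions, the false-positive rate with 10 per arm would be about 10% to 26% instead of 9%.

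It would go too far to say that the sham-controlled, dose and biomarker claims all fail. VA2 versus SA is unaffected by session number, and VA1 versus VA2 remains a valid comparison of regimens. Nor does equal session number make VA2 and SA alike in every other respect. Verum participants may receive 6 to 19 points, with optional points chosen by symptoms (section 2.8.1), while SA receives 6 fixed points (section 2.8.4). The matching claimed for VA2 versus SA should therefore be limited to sessions. The rating is should-fix.

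**What to change.** 1. In sections 2.11.2 and 2.10.14, name VA2 versus SA in advance as the session-matched sham-controlled contrast, whichever verum arm looks better.
2. Report VA1 versus SA and VA1 versus VA2 as effects of the regimen including visit frequency, and do not present VA1 versus SA as a specific effect of needling. Where effect sizes feed the power calculation for the large trial, say which contrast each comes from.
3. In the Discussion, correct the rationale for the sham session number and state that VA1 versus SA is not matched on contact. The sentence on common outcome measures can stay if it is expressly limited to attention from outcome assessment.

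The cost is wording only, with no new data and no change to the treatment schedule. The small downside is that VA1 can no longer carry the sham-controlled claim, even if it gives the larger difference.

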## Figures and Tables

**Figure 1 fig1:**
[figure not shown]
*Flow of the trial*. (a) Randomisation schema for participants with AD. (b) Recruitment of healthy controls for comparative microRNA expression profiling analysis against AD patients. AD, atopic dermatitis; CES-D, Centre for Epidemiologic Studies-Depression Scale; Cold-Heat, questionnaire of cold-heat pattern identification based on diagnosis in Traditional Korean Medicine; DLQI, Dermatology Life Quality Index; EASI, Eczema Area and Severity Index; POEM, Patient Oriented Eczema Measure; PPT, Pressure Pain Threshold; SCORAD, SCORing Atopic Dermatitis; STAXI, state-trait anger expression inventory; VAS, Visual Analogue Scale.

**Figure 2 fig2:**

*Flow of Illumina sequencing*. AD, atopic dermatitis; VA, among VA1 and VA2, the most effective schema will be selected; SA, sham acupuncture group; wks, weeks. A tube icon means the sera obtained from the blood samples.

**Table 1 tab1:** Acupuncture treatment details based on the STRICTA 2010 checklist.

Item	Detail
*(1) Acupuncture rationale*	*(1a) Style of acupuncture* (i) MA and IA using PTN based on traditional meridian theory *(1b) Reasoning for treatment provided, based on historical context, literature sources, and/or consensus methods, with references where appropriate* (i) Partially individualised MA treatments and IA treatments based on the traditional meridian theory, clinical experience, and consensus by the experts in acupuncture and AD *(1c) Extent to which treatment was varied* *MA*: Partially individualised, that is, fixed points plus optional points according to symptoms *IA*: Fixed treatment

*(2) Details of needling*	*(2a) Number of needle insertions per subject per session (mean and range where relevant)* *MA*: From 6 to 19 body acupoints per participant per session *IA*: 2 body acupoints and 1 auricular acupoint per participant per session *(2b) Names (or location if no standard name) of points used (uni/bilateral)* *MA*: (i) Fixed points: PC6, LI11, ST36 bilaterally (ii) Optional points: ST43, GB41, LI2, TE3, TE6, SI2, SI3, BL66, LR3, SP3 contralaterally (GB41, TE3, SI3 can be applied bilaterally according to the signs or symptoms of the patient) *IA*: LI11 bilaterally and auricular shenmen contralaterally *(2c) Depth of insertion, based on a specified unit of measurement or on a particular tissue level* *MA*: From 5 to 30 mm, perpendicular to skin surface *IA*: 1.5 mm, perpendicular to skin surface *(2d) Response sought (e.g., de qi or muscle twitch response)* *MA*: “de qi” sensation *IA*: None *(2e) Needle stimulation (e.g., manual, electrical)* *MA*: Manual stimulation, needle rotation with thumb and index fingers for the first 10–15 seconds *IA*: Participants will be educated to press PTNs for 3 seconds when they feel severe itch *(2f) Needle retention time* *MA*: 15 minutes *IA*: 1-2 days or until PTN falls off *(2g) Needle type (diameter, length, and manufacturer or material)* *MA*: A sterilised stainless steel needle (0.25 × 40 mm, Dongbang Acupuncture Inc., Bundang, Seongnam, Korea) *IA*: A hypoallergenic PTN (1.5 mm, 10 × 10 mm adhesive tape, Haeng Lim Seo Won Medical Co., Korea)

*(3) Treatment regimen*	*(3a) Number of treatment sessions* (i) 8 or 12 sessions according to the allocated group *(3b) Frequency and duration of treatment sessions* (i) Twice or 3 times a week for 4 weeks, 20 minutes for each session

*(4) Other components of treatment*	*(4a) Details of other interventions administered to the acupuncture group (e.g., moxibustion, cupping, herbs, exercises, lifestyle advice)* (i) Lifestyle advices will be given to all participants (ii) Corticosteroids will be allowed as a rescue medicine of severe pruritus through the consensus of the KMD in charge of this study and the pharmacist working for Kyung Hee University Korean Medicine Hospital *(4b) Setting and context of treatment, including instructions to practitioner and information and explanations to patients* (i) A university hospital (ii) Participants will be informed about acupuncture treatment in the study as follows: “In this study, you will be randomly allocated to verum acupuncture treatment or sham acupuncture treatment and acupoints for AD will be selected based on traditional Korean medicine textbook and AD-related reports. Also, additional acupoints can be used according to individual conditions.”

*(5) Practitioner background*	*(5) Description of participating acupuncturists (qualification or professional affiliation, years in acupuncture practice, other relevant experience)* (i) A KMD who has a license and at least two years of clinical experience in dermatologic disorders. He attended 10 hours of training and simulation workshop to ensure that he is able to provide identical acupuncture treatment in accordance with a predefined protocol

*(6) Control or comparator interventions*	*(6a) Rationale for the control or comparator in the context of the research question, with sources that justify this choice* (i) A control group will be treated with sham acupuncture, that is, Park sham acupuncture needles and nonpenetrating sham PTNs *(6b) Precise description of the control or comparator. If sham acupuncture or any other type of acupuncture-like control is used, provide details as for items (1) to (3) above* *MA*: Park sham acupuncture needles and devices will be used in an identical manner as in the verum acupuncture groups. However, fixed acupuncture treatments will be given to 6 control points: a point 1 to 2 cm proximal and 1 cm medial to LI7, a point 1 cm proximal and 1 cm medial to LI11, and a point 1 cm proximal and 1 cm lateral to ST36, each bilaterally *IA*: Nonpenetrating sham PTNs, which were designed and validated for blinding for our study, will be used as a control in an identical manner as in the verum acupuncture groups. The same sized stainless steel rings without needles, that is, nonpenetrating sham, which were designed and validated for blinding for our study, will be attached to three control points: a point 1 cm proximal and 1 cm medial to LI11, bilaterally, and finger point in the ear, contralaterally

AD, atopic dermatitis; IA, intradermal acupuncture; KMD, Korean Medicine Doctor; MA, manual acupuncture; PTN, press tack needle; STRICTA, STandards for Reporting Interventions in Clinical Trials of Acupuncture.

**Table 2 tab2:** Study schedule for data collection, treatments, and outcome measures.

Treatment and measures	Baseline	Treatment period				Follow-up period			
		1-week	2-week	3-week	4-week	5-week	6-week	7-week	8-week
Demographics	●								
Physical examination	●								
Medical history	●								
Visual Analogue Scale for itch	○	○	○	○	○		☏		○
SCORAD assessment	○	○	○	○	○				○
EASI assessment	○	○	○	○	○				○
POEM assessment	○	○	○	○	○				○
DLQI assessment	○	○	○	○	○				○
TCS evaluation	○	○	○	○	○		☏		○
AD pattern questionnaire	○								
Cold-Heat questionnaire	●								
PPT evaluation	○		○		○				
CES-D assessment	●				○				○
STAXI assessment	●				○				○
Credibility test	○				○				○
Acupuncture treatment		⊗	⊗	⊗	⊗				
Adverse events		⊗	⊗	⊗	⊗		☏		○
Blood collection	●				○				○

●: conducted on every participant of this study, both AD patients and healthy controls; ○: conducted on AD patients of this study, not on healthy controls; ⊗: conducted on AD patients, but with different frequency on groups. That is, VA1 receives acupuncture treatment or checks adverse events 3 days a week, VA2 2 days a week, and SA 2 days a week; ☏: a telephone interview will be conducted on AD patients of this study, not on healthy controls; AD, atopic dermatitis; CES-D, Center for Epidemiologic Studies-Depression Scale; Cold-Heat, cold-heat pattern identification based on diagnosis in Traditional Korean Medicine; DLQI, Dermatology Life Quality Index; EASI, Eczema Area and Severity Index; POEM, Patient Oriented Eczema Measure; PPT, Pain Pressure Threshold; SCORAD, SCORing Atopic Dermatitis; STAXI, state-trait anger expression inventory; TCS, topical corticosteroid.

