## 2. Materials and Methods

### 2.1. Objectives

The aims of this study are (1) to investigate the feasibility of a large-scale randomised clinical trial to test the antipruritic effect of acupuncture treatment compared with a sham acupuncture in patients with AD; (2) to identify the optimal dose and schedule of acupuncture treatment and to identify outcome measures that will reflect symptoms changes; and (3) to discover biomarkers that may be associated with the therapeutic effects of acupuncture.

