#### 2.12.2. Participant Safety

During each visit, unanticipated problems or adverse events related to acupuncture treatment will be reported by participants and documented by study staff. Acupuncture treatment has been reported as a safe treatment rarely causing adverse effects; common adverse effects caused by acupuncture treatment include bleeding, hematoma, and pain [66]. Any unfavourable or unexpected signs related to study treatment or procedures will be compiled on paper, managed under the care of practitioners, and reported to institutional and other oversight agencies as appropriate.

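### Adverse events are checked 12 times in VA1 but 8 times in VA2 and SA, so recorded events can be inflated in VA1 and cannot be separated from its greater exposure

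*Protocol article*

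**What the plan says.** The adverse-event row of Table 2 carries, for weeks 1 to 4, the symbol that the footnote defines as "conducted on AD patients, but with different frequency on groups". The footnote then gives the frequencies: "VA1 receives acupuncture treatment or checks adverse events 3 days a week, VA2 2 days a week, and SA 2 days a week".

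These match the session counts in sections 2.8.2 to 2.8.4: "Participants assigned to the VA1 will receive 12 acupuncture sessions over 4 weeks, that is, 3 days/week"; "Participants assigned to the VA2 will receive 8 acupuncture sessions over 4 weeks, that is, 2 days/week"; "Participants assigned to the SA group will receive 8 acupuncture sessions over 4 weeks, that is, 2 days/week".

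Section 2.12.2 ties collection to attendance: "During each visit, unanticipated problems or adverse events related to acupuncture treatment will be reported by participants and documented by study staff". It states no recall period.

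After treatment the arms are handled alike. Each has a telephone interview at week 6 "to collect data on the severity of pruritus symptoms, amount of TCS used, and adverse effects" and a visit at week 8.

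Table 2 schedules itch VAS, SCORAD, EASI, POEM, DLQI and TCS use weekly in every AD arm during treatment. Apart from the treatment itself, adverse events are the only row whose frequency depends on the arm.

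One aim in section 2.1 is "to identify the optimal dose and schedule of acupuncture treatment and to identify outcome measures that will reflect symptoms changes".

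**The concern.** The number of times a patient is asked about adverse events rises with the treatment frequency under comparison. Section 2.12.2 expects bleeding, haematoma and pain. If such events are minor and short-lived, they may be forgotten between visits, and an arm asked more often can then record more of them at the same true rate.

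VA1 also receives more needling, and in the same proportion as it receives more enquiries. A higher count in VA1 could come from either source, and the data as scheduled give no way to divide it.

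At stake is how well tolerated three sessions a week look beside two. The Discussion says that patients' acceptability should be weighed when the two schedules are compared, and adverse events bear on that.

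**Working it through.** **Inputs from the article.** Checks on 3 days a week in VA1 and 2 in VA2 and SA (Table 2 footnote); 4 treatment weeks and 12, 8 and 8 sessions (sections 2.8.2 to 2.8.4); 30 AD patients allocated 1:1:1, so 10 per arm; one telephone call and one final visit in every arm.

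**Assumed, because the article gives no figure.** The event rate, how fast recall fades, and the weekdays of visits.

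**1. Number of checks.** 3 × 4 = 12 and 2 × 4 = 8, which reproduces the stated sessions. The ratio is 12/8 = 1.5. With the two common follow-up contacts it is 14/10 = 1.4. These counts are for full attendance.

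**2. Equal true rate, fading recall.** Suppose events occur at the same daily rate in both arms, and an event is reported at the next check with probability exp(−lag/τ). Take visits on Monday, Wednesday and Friday in VA1 (gaps of 2, 2 and 3 days) and on Monday and Thursday in VA2 (gaps of 3 and 4 days). The share of events recorded is Σ τ(1 − exp(−gap/τ)) / 7, summed over the gaps in a week.

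For τ = 1 day:
- VA1: (0.865 + 0.865 + 0.950)/7 = 0.383
- VA2: (0.950 + 0.982)/7 = 0.276
- Ratio: 0.383/0.276 = 1.39

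| τ | VA1 share | VA2 share | Ratio |
|---|---|---|---|
| 1 day | 0.383 | 0.276 | 1.39 |
| 2 days | 0.583 | 0.469 | 1.24 |
| 3 days | 0.688 | 0.587 | 1.17 |
| 7 days | 0.846 | 0.784 | 1.08 |
| complete recall | 1.000 | 1.000 | 1.00 |

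**3. How often this shows with 10 per arm.** With one true event per patient over the treatment period and Poisson counts (200,000 simulated trials per setting), VA1 records more events than VA2 in 51.2% (τ = 7) to 58.5% (τ = 1) of trials and fewer in 39.0% to 26.8%. With complete recall the two are level (45.3% and 45.6%).

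**4. Why enquiry and exposure cannot be separated.** Suppose instead that each visit yields a report with probability p. The chance that a patient has at least one report is 1 − (1 − p)^k, with k = 12 or 8.

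| p | VA1 (k = 12) | VA2 or SA (k = 8) | Ratio |
|---|---|---|---|
| 0.02 | 21.5% | 14.9% | 1.44 |
| 0.05 | 46.0% | 33.7% | 1.37 |
| 0.10 | 71.8% | 57.0% | 1.26 |
| 0.20 | 93.1% | 83.2% | 1.12 |

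This table is the same whether p is the risk of harm from one session or the yield of one enquiry, because sessions and enquiries are both 12 against 8. The observed counts cannot tell the two apart.

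**5. Under a common weekly question.** Every arm has 4 enquiries in treatment plus 2 in follow-up, 6 against 6, a ratio of 1.0. What remains is the real difference in exposure, 12 against 8 sessions, which a per-session rate shows directly.

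**The case against.** Several points on the other side have force.

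- **Recall may be adequate.** Under the assumed visit days the gaps are 2 to 4 days, and a question covering the time since the last visit could span them. The full protocol or case report form may word it that way. This stands as a limit on size: with complete recall the ratio is 1.0. It does not remove the unequal schedule, which the article itself fixes.
- **The expected events come from needling.** At equal risk per session, VA1 truly has 1.5 times the events per patient. That is a consequence of the schedule and no artefact. This stands, and it is why the point concerns two effects that cannot be separated and not a pure detection bias.
- **The choice of regimen rests on efficacy.** A reader might infer that inflated counts will drive the dose taken forward. The text does not support that: section 2.11.2 compares VA1 with VA2 on itch VAS and SCORAD, sections 2.10.14 and 2.11.2 carry forward the more efficacious arm, and no between-arm safety test is announced.
- **Follow-up and flares.** A reader might add that nothing is asked between the last session and week 6, or that the relatedness wording of section 2.12.2 would lose skin flares. The first interval is the same in all arms, so it cannot bias one against another. A flare would appear in the weekly SCORAD, EASI, POEM and TCS records whatever the patient attributes it to.

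**Conclusion.** The point holds as a caution on the descriptive tolerability comparison. The schedule of 12 checks against 8 is stated outright, and nothing in the article offsets it. With equal true rates, the expected ratio of recorded events, VA1 to VA2, lies between 1.0 and about 1.4, depending on assumed recall and assumed visit days. The same applies to VA1 against SA as far as frequency of asking goes. VA2 against SA is unaffected, since both are checked twice a week.

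A reader might infer that VA1 will show more adverse events, or that the excess will be 1.5-fold. Neither follows. The article gives no event rate or recall period; 1.5 is the ratio of checks, which recorded events would approach only if recall faded almost at once; and with 10 patients per arm chance can reverse the order.

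**What to change.** For between-arm safety summaries, ask every AD patient one standard adverse-event question with the same 7-day recall at the weekly assessment that Table 2 already schedules in all arms (weeks 1 to 4). Ask about all events whatever their cause, and have the investigator judge relatedness, so that the comparison does not depend on what the patient attributes to needling.

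Keep the per-session checks for patient care. Report the events they yield per session delivered as well as per patient, so that exposure is visible. Change the Table 2 footnote and section 2.12.2 to say which source serves which purpose.

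The cost is one added question a week and two edits of wording, with no extra visit. Formal enquiry becomes equal, but VA1 patients still attend more often, and some prompting from those visits may carry over into their weekly answers. The report should say so.
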